### 1.2.1 Justification for participant population

The target population in this trial is limited to adults with no upper age restriction. This is because ISSNHL is very rare in children, they have a different risk-profile to adults and there are implications around the practicalities of oral and intratympanic steroid use in children. .

The trial population includes women of child bearing potential. As with all drugs, corticosteroids should only be prescribed to pregnant women when the benefits to the mother and child outweigh the risks. Short-course high dose steroids are a low risk intervention in pregnant women. While old data had suggested that systemic corticosteroid use during pregnancy increases the risk of cleft lip/palate, preterm birth or low birth weight (5), recent studies have confirmed there is no independent association seen in the US National Birth Defect prevention Study (6,7). Maternal risks of corticosteroid specific side-effects such as hyperglycaemia and hypertension are similar to non-pregnant patients (e.g.) (8). Therefore, pregnant women are not excluded from this study. A discussion of the risks and benefits of steroids in pregnancy should take place if the study participant could be pregnant, as is standard clinical practice.

Participants with an identified cause for hearing loss or bilateral ISSNHL will be excluded as the intervention arms may not represent best care. Those with prior steroid treatment for the same episode of ISSNHL will also be excluded due to the risk of confounding treatment effects. Ipsilateral acute or chronic middle ear disease including acute otitis media, chronic suppurative otitis media and cholesteatoma will lead to exclusion as injected steroids may not reach the inner ear.

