## **7.7 Intervention modification or cessation**

As specified in section 7.3, complete resolution of hearing may allow intratympanic steroid treatment to be terminated after only one or two treatments. A rare complication of intratympanic injection is further hearing loss. Where this is observed on pure tone audiometry, no further treatments will be given. In the rare event that a study participant chooses to change treatment type or has a significant side effect from oral steroids and is advised to modify or stop the treatment by their treating clinician this will be recorded. On rare occasions, changes to the intervention schedule may be required based on participant request or adverse events. The allocated interventions may be discontinued if a participant requests to cease treatment or cross over to another arm. Adverse events such as allergic reaction, or a change in patient status, such as development of poor blood glucose control may alter the risk-benefit profile for that individual and the treating clinician should discuss this with the patient and alter the provided intervention, if required. Details of treatment

---

adherence, treatment modifications or treatment discontinuation at the Investigator's discretion should be documented in the source data.

Any modification of the interventions, or cross over to another trial arm will also be recorded on the CRFs.

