## 8.2 Main Trial Outcomes

### 8.2.1 Primary Outcome

- **The absolute improvement in pure tone audiogram average at 12 weeks** following randomisation (calculated at 0.5, 1.0, 2.0, 4.0 kHz). Conducted by an audiologist blinded to the treatment allocation.

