|                              | Severe   | Incapacity with inability to do work or perform usual activities.                                                                                                                                                                                                                                                                                                                                                                                                                                     |
| Adverse Event         | AE       | 
Any untoward medical occurrence in a participant or clinical trial subject administered a medicinal product and which does not necessarily have a causal relationship with this treatment.
 
Comment:
 
An AE can therefore be any unfavourable and unintended sign (including abnormal laboratory findings), symptom or disease temporally associated with the use of an investigational medicinal product, whether or not related to the investigational medicinal product.
 |
| Adverse Reaction      | AR       | 
All untoward and unintended responses to an IMP related to any dose administered.
 
Comment:
 
An AE judged by either the reporting Investigator or Sponsor as having causal relationship to the IMP qualifies as an AR. The expression reasonable causal relationship means to convey in general that there is evidence or argument to suggest a causal relationship.
                                                                                                        |
| Serious Adverse Event | SAE      | 
Any untoward medical occurrence or effect that:
 

● Results in death

● Is life-threatening*

● Requires hospitalisation or prolongation of existing hospitalisation

● Results in persistent or significant disability or incapacity

● Is a congenital anomaly/birth defect

                                                                                                                                        |

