## 10.3 Adverse Event reporting in STARFISH

The safety profile for this trial population and interventions are well characterised so a strategy of targeted reporting of AEs will not affect the safety of participants.

Only the following AEs will be reported on the 6 week follow up CRF:

- 
- Further sudden deterioration of hearing after intervention
  - Affective disorders
  - Psychotic reactions
  - Stomach ulcer
  - Acute ear infection (otitis externa or media)
  - New dizziness onset or worsening after intervention
  - New tinnitus onset or worsening after intervention
  - Persistent ear drum perforation at 6 week review
  - Allergic reaction to steroid preparation
  - Allergic reaction to local anaesthetic

Only the following AEs will be reported on the 12 week follow up CRF:

- Persistent perforation of the tympanic membrane

The reporting period for AEs will be from commencement of trial treatment until the 12 week follow up visit (see above for further details of timeline requirements of AE reporting).

The reporting period for Serious Adverse Events (SAEs) will be from commencement of trial treatment until 6 weeks post treatment commencement. All AEs which meet the SAE definition should be reported as per section 10.4.

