#### 10.4 Serious Adverse Event reporting in STARFISH

All events which meet the definition of serious, must be recorded in the participant notes, including the causality and severity, throughout the participant's time on trial, including follow-up.

For all SAEs, the PI or delegate must do one of the following:

- **Record safety reporting-exempt SAEs** in the medical notes but **not report** them to BCTU on an SAE form as per Section 10.4.1
- **Report SAEs to BCTU in a non-expedited manner.** This can only be done for the pre-defined subset of AEs as per Section 10.4.2. These should be reported in line with the expected timeframes for other CRFs, i.e. within 4-weeks of becoming aware of the event.
- **Report SAEs to BCTU in an expedited manner** i.e. within 24 hours of the site research team becoming aware of the event. All SAEs not covered by the above two categories must be reported as per Section 10.5

**Note:** when an SAE occurs at the same hospital at which the participant is receiving trial intervention or is being followed up for trial purposes, processes must be in place to make the trial team at the hospital aware of any SAEs, regardless of which department first becomes aware of the event, in an expedited manner.

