### 10.6.2 MHRA, REC and RGT

BCTU will report details of all SARs (including SUSARs) to the Medicines and Healthcare Products Regulatory Agency (MHRA), Research Ethics Committee (REC) and UoB Research Governance Team (RGT) annually from the date of the Clinical Trial Authorisation, in the form of a Development Safety Update Report (DSUR).

In addition, BCTU will report a minimal data set of all individual events categorised as a fatal or life threatening SUSAR to the MHRA, REC and RGT within 7 days of being notified. Follow-up information will be provided within an additional 8 days.

All other events categorised as non-life threatening/non-fatal SUSARs will be reported within 15 days of being notified.

The MHRA, REC and RGT will be notified immediately if a significant safety issue is identified during the course of the trial.

Details of all SUSARs and any other safety issues which arise during the course of the trial will be reported to PIs. A copy of any such correspondence should be filed in the ISF and Trial Master File (TMF).

---

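### Section 10.3 stops SAE reporting at 6 weeks while sections 10.4, 10.4.1 and 10.6.2 set no such limit, so a related SAE after week 6 has no settled route to the trials unit

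*Protocol*

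**What the plan says.** Section 10.3 sets two reporting periods. For adverse events: "The reporting period for AEs will be from commencement of trial treatment until the 12 week follow up visit". For serious events: "The reporting period for Serious Adverse Events (SAEs) will be from commencement of trial treatment until 6 weeks post treatment commencement". The sentence after that sends every AE that meets the SAE definition to section 10.4 for reporting. The section justifies its targeted approach for AEs by the known safety profile; it gives no separate reason for the SAE cut-off.

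Section 10.4 says that serious events "must be recorded in the participant notes, including the causality and severity, throughout the participant's time on trial", and it includes follow-up in that time. It then requires the site, for all SAEs, to take one of three routes: exempt, non-expedited or expedited. Section 10.4.3 puts everything outside the first two routes on a 24-hour report. Section 10.4.1 defines the exempt events for a period running from consent to the end of follow-up.

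Section 10.6.2, on the annual report to the regulator, ethics committee and research governance team, says: "BCTU will report details of all SARs (including SUSARs". No time limit is attached.

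In section 9, the week 6 visit (±7 days, counted from randomisation) includes AE and SAE monitoring. The week 12 visit lists only AE monitoring, for the two injected arms and for persistent eardrum perforation alone. Table 3 and its footnote say the same.

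**The concern.** A site that judges an SAE at week 8 to be related to treatment can read the protocol in two ways. Under section 10.3 the reporting period has closed. Under sections 10.4 and 10.4.3 a report is due within 24 hours. The protocol does not say which section governs, and it has no sentence on related SAEs that arise, or become known, after week 6.

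If the site follows section 10.3, the event stays in the notes. The causality review (10.5.1), the expectedness review that identifies a SUSAR (10.5.2), the DMC (10.6.1) and the annual safety report (10.6.2) all depend on the trials unit receiving it. The unit cannot report all serious adverse reactions if sites need not send it some of them.

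The AE and SAE periods also conflict. A perforation that becomes serious between weeks 6 and 12 is inside the AE period and outside the SAE period, although section 10.3 itself says that AEs meeting the SAE definition are to be reported.

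**Working it through.** The protocol states no figure to reproduce here. The check is a comparison of sections and some calendar arithmetic.

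**Which sections limit SAE reporting in time**

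| Section | Duty | Time limit stated |
|---|---|---|
| 10.3 | SAE reporting period | 6 weeks from start of treatment |
| 10.3, next sentence | AEs meeting the SAE definition go to 10.4 | none |
| 10.4 | record in notes, with causality and severity | whole time on trial, including follow-up |
| 10.4, 10.4.3 | report all non-exempt SAEs | none |
| 10.4.1 | defines exempt events | consent to end of follow-up |
| 10.6.2 | report all serious adverse reactions | none |

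Exemptions that run to the end of follow-up would serve no purpose after week 6 if nothing were reportable then. This suggests that section 10.4 was written with the whole follow-up in mind.

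**How much of follow-up the window covers**

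Inputs: window 6 × 7 = 42 days from first treatment (10.3); "The absolute improvement in pure tone audiogram average at 12 weeks" from randomisation, so 12 × 7 = 84 days (8.2.1); visit window ±7 days (section 9), so day 77 to 91. Assumption: treatment starts on the day of randomisation. Section 5.1 asks for both on the same or next working day after consent, ideally.

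- Share covered: 42/84 = 50%; range 42/91 = 46% to 42/77 = 55%.
- Days after the window closes: 84 − 42 = 42; range 77 − 42 = 35 to 91 − 42 = 49.

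**How the week 6 visit fits the window**

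The visit may fall from day 42 − 7 = 35 to day 42 + 7 = 49.

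- Visit on day 49: 49 − 42 = 7 days have passed since the window closed. An SAE that began in those days is found at a visit meant to look for SAEs, yet lies outside the period.
- Visit on day 35: 42 − 35 = 7 days of the window remain. No later visit asks about SAEs, because week 12 collects only persistent perforation in the injected arms.

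If treatment starts d days after randomisation, the window closes on day 42 + d. The first gap becomes 7 − d days and the second 7 + d.

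**The case against.** The strongest defence is that the event is not lost. It must be in the notes with its causality. Section 10.4, read literally, still requires a report, section 10.2 ties recording and reporting to the UK clinical trials regulations, and section 10.6.2 requires immediate notice of a significant safety issue. This stands as far as it goes: no reader should conclude that late SAEs are certain to go unreported. But it rests on one of two available readings. If section 10.3 sets the window and section 10.4 only the procedure, a related SAE at week 8 has no stated route, and the trials unit can act only on what it receives.

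A 6-week limit can also be defended in itself. The trial is rated Type A risk, the drugs are well characterised, and treatment courses are short. That supports a limit for unrelated SAEs. It does not explain why related ones are not excepted.

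Some stronger readings are tempting but not supported:

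- **Bias between arms.** Time after the last planned dose does differ: 42 − 6 = 36 days for oral, and nominally 42 − 14 = 28 for intratympanic. But every arm has the same 42 days from the start of treatment, so SAE proportions are compared over equal time. Running to day 84 would give 78 and 70 days, the same 8-day difference, because it comes from the treatment schedules. Counting the window from the last dose would give the arms unequal windows.
- **An unobserved second half.** Week 12 has otoscopy, audiometry and questionnaires in all arms, and section 15.2 adds a participant questionnaire on health-service contacts. None is an SAE review, but the period is not unobserved.
- **Pregnancy.** Section 1.2.1 says "Therefore, pregnant women are not excluded from this study", and the SAE criteria in section 10.1 include "Is a congenital anomaly/birth defect". Section 10.8, however, gives reasons for planning no extra follow-up of pregnancy outcomes. That is a stated choice.
- **Late cross-over.** Section 7.7 says "The allocated interventions may be discontinued if a participant requests to cease treatment or cross over to another arm", but gives no timing and presents a change of treatment type as rare. Exposure close to or after the cut-off would be conjecture.

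**Conclusion.** The point holds as a contradiction within the safety section. The SAE period in section 10.3 ends at about half of follow-up (50%; 46% to 55%), with no exception for related events, while sections 10.4, 10.4.1, 10.4.3 and 10.6.2 carry no such limit. A related SAE arising or becoming known in the remaining 35 to 49 days may not reach the trials unit, the chief investigator's review, the DMC or the annual safety report. The week 6 check can also miss the end of the window by up to 7 days in either direction.

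The day counts assume that treatment starts on the day of randomisation. How many events are affected cannot be said, since the protocol gives no late SAE rate, and it may be few. The efficacy analysis is untouched, and the SAE comparison between arms is not shown to be biased. It is a patient-safety matter that is cheap to put right and should be corrected.

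**What to change.** Reconcile section 10.3 with sections 10.4, 10.4.1 and 10.6.2:

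1. State that any SAE considered related to trial treatment is reportable to the trials unit whenever the site becomes aware of it.
2. Add an SAE review line to the week 12 visit in section 9 and in Table 3, for all three arms.
3. Choose one of two periods and use it throughout section 10: either extend the SAE period to the 12-week visit, in line with the AE period, or keep the 6-week limit for unrelated SAEs only.

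Extending the period adds about 42 days of SAE reporting (35 to 49 with the visit window). With either choice, the week 12 line picks up SAEs from the end of the 6-week window that an early week 6 visit would miss.

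The cost is a change of protocol wording, one line on the 12-week form and a few more SAE forms. Participants already attend at week 12, and sites already have to record these events with their causality.

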#### 10.4 Serious Adverse Event reporting in STARFISH

All events which meet the definition of serious, must be recorded in the participant notes, including the causality and severity, throughout the participant's time on trial, including follow-up.

For all SAEs, the PI or delegate must do one of the following:

- **Record safety reporting-exempt SAEs** in the medical notes but **not report** them to BCTU on an SAE form as per Section 10.4.1
- **Report SAEs to BCTU in a non-expedited manner.** This can only be done for the pre-defined subset of AEs as per Section 10.4.2. These should be reported in line with the expected timeframes for other CRFs, i.e. within 4-weeks of becoming aware of the event.
- **Report SAEs to BCTU in an expedited manner** i.e. within 24 hours of the site research team becoming aware of the event. All SAEs not covered by the above two categories must be reported as per Section 10.5

**Note:** when an SAE occurs at the same hospital at which the participant is receiving trial intervention or is being followed up for trial purposes, processes must be in place to make the trial team at the hospital aware of any SAEs, regardless of which department first becomes aware of the event, in an expedited manner.

##### 10.4.1 Serious Adverse Events not requiring reporting to BCTU

At whatever time they occur during an individual's participation, from consent to end of participant follow up, the following are not considered to be critical to evaluations of the safety of the trial:

- a) Pre-planned hospitalisation
- b) Hospitalisations lasting less than 24hrs

---

Such events are “safety reporting exempt”.

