#### 10.4.2 Serious Adverse Events requiring non-expedited reporting to BCTU

Where the safety profile is well established, the causal relationship between the intervention (or the participant’s underlying condition) and the SAE, may be known. That is, such events are protocol-defined as “expected”.

Such events should still be recorded in the participant’s medical notes and reported to BCTU on the SAE form (as per section 10.5) but it does not require expedited reporting (immediately on the site becoming aware of the event) since the assessment of expectedness for the specified events has been pre-defined. These should be reported in line with the expected timeframes for other CRFs, i.e. within 4-weeks of becoming aware of the event. These events are detailed in Table 5 below.

**Table 5:** Expected SAEs in STARFISH

| Expected events related to oral steroids                  | Expected events related to intratympanic injection      | Expected events related to both oral steroids and intratympanic injection |
|-----------------------------------------------------------|---------------------------------------------------------|---------------------------------------------------------------------------|
| Blood glucose derangement requiring hospitalisation       | Complete sensorineural hearing loss following injection | Allergic reaction requiring hospital treatment                            |
| Psychotic or affective disorder requiring hospitalisation |                                                         |                                                                           |

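### The exemption for hospital stays under 24 hours in section 10.4.1 has no relatedness condition and conflicts with Table 5, 10.5.2 and 10.6.2

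*Protocol*

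**What the plan says.** The SAE definition in section 10.1 (Table 4) includes an event that "Requires hospitalisation or prolongation of existing hospitalisation", with no minimum length of stay. Section 10.4 requires that "All events which meet the definition of serious, must be recorded in the participant notes, including the causality and severity", and then sends each SAE down one of three routes: notes only, SAE form within four weeks, or SAE form within 24 hours.

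The notes-only route is defined in 10.4.1. From consent to the end of follow-up, "the following are not considered to be critical to evaluations of the safety of the trial": pre-planned admissions, and "Hospitalisations lasting less than 24hrs". Nothing further qualifies the second item.

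The four-week route (10.4.2) covers the expected events in Table 5, such as "Allergic reaction requiring hospital treatment". The 24-hour route (10.4.3) takes whatever is in neither 10.4.1 nor 10.4.2.

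Downstream, 10.5.1 starts the independent causality review when an SAE form is received. Section 10.5.2 has the Chief Investigator or delegate assess every SAR for expectedness. Section 10.6.2 states that "BCTU will report details of all SARs (including SUSARs) to the Medicines and Healthcare Products Regulatory Agency (MHRA"), the REC and the sponsor's governance team each year, with SUSARs going sooner, within 7 or 15 days of BCTU being notified. None of these sections carves out the exempt events.

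**The concern.** The exemption turns on how long the participant stayed in hospital, while the duties that follow turn on whether the event was caused by treatment. The two do not line up. A related event with a short admission is a SAR by the protocol's own definitions, and BCTU undertakes to assess and report it, yet the site is told not to submit the form on which that assessment depends.

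At stake is the completeness of SAR and SUSAR reporting to the regulator and the ethics committee, and of the SAE data that the Data Monitoring Committee may review under 10.6.1. The efficacy analysis is not affected.

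**Working it through.** The protocol states no figure on this point, so the check sets the sections side by side.

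**Can an exempt event be a SAR?** Yes. Section 10.1 has no minimum stay, so an admission of, say, 20 hours is an SAE. Table 4 defines a SAR as an adverse reaction that also meets the SAE definition. Section 10.5.1 tells sites to apply the related/unrelated categories to exempt SAEs in the source data, so the protocol itself foresees an exempt event classed as related.

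**Does it reach central review?** Section 10.4 says exempt SAEs are not reported on an SAE form, 10.4.3 leaves them out of expedited reporting, and 10.5.1 makes receipt of a form the trigger for causality review. On this route no trigger occurs.

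**Four cases, each an admission of 20 hours within the SAE reporting window of 10.3:**

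1. *Table 5 event, for example glucose derangement.* 10.4.1 says no form; 10.4.2 says a form within four weeks. Section 10.4 requires one route and gives no order of precedence. Three of the four Table 5 entries are worded in terms of hospitalisation or hospital treatment (glucose, psychotic or affective disorder, allergic reaction), so the overlap is direct.
2. *Related event outside Table 5 but on the 6-week AE list, for example stomach ulcer.* 10.4.1 says no form. BCTU learns of the event from the 6-week CRF, for which the protocol describes no central causality or expectedness review. By the protocol's own windows this could be as late as 6 weeks + 1 week (visit window) + 4 weeks (data submission, 11.2) = 11 weeks after randomisation, against 24 hours under 10.4.3.
3. *Related event in neither Table 5 nor the 6-week list.* No form and no CRF item. If unexpected it is a SUSAR under 10.5.2, but the 7- or 15-day period in 10.6.2 runs from BCTU being notified and so would not start.
4. *Unrelated event meeting no other seriousness criterion.* 10.4.1 applies and nothing conflicts with it.

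**How much does the 6-week CRF recover?** Of its ten items, the affective, psychotic and two allergic items, together with further sudden deterioration of hearing, correspond to three of the four Table 5 entries. Glucose derangement is the one Table 5 entry with no counterpart (0 of 10 items).

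The contradiction therefore lies in cases 1 to 3. Possible central loss of the event is confined to case 3, and to glucose derangement in case 1 if sites let 10.4.1 prevail.

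**The case against.** The strongest reply is that the exemption loses less than it seems to. Section 10.4 withholds only the SAE form. Allergic reactions, psychotic reactions, affective disorders and stomach ulcer are all on the 6-week CRF, so BCTU hears of them. Table 5 events must still be reported under 10.4.2, and a sensible site may follow that. An event that is serious on another ground, such as being life-threatening, can reasonably be read as falling outside an item that speaks only of hospitalisation. All of this stands. It limits the consequence, but it does not remove the conflict: hearing of an event on a CRF is not the causality and expectedness review promised for every SAR, and the reading that saves Table 5 is one the site has to supply.

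A reader might infer more than the text supports, in three ways.

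- *That every related stay under 24 hours is lost.* This assumes that 10.4.1 always overrides Table 5. The protocol does not say so, and the contradiction consists in its saying both things.
- *That leaving glucose off the AE list is an error that tilts the comparison of routes.* Section 10.3 says "Only the following AEs will be reported on the 6 week follow up CRF" and justifies targeted reporting by a well-characterised safety profile, so the list is a stated design choice. Three of its ten items are systemic (affective, psychotic, ulcer) and steroid allergy can arise in any arm. Only Table 5 ties glucose harm to oral steroids specifically. Section 7.6.2 speaks of both routes, and 7.7, where "development of poor blood glucose control may alter the risk-benefit profile for that individual", names no route. Treatment changes go on the CRF under 7.7, and resource use from adverse events is collected under 15.2. What is not itemised is non-serious derangement.
- *That recording 12-week perforation only in the two injection arms is a mistake.* Section 9 and Table 3 state it consistently, and at 6 weeks the item covers all arms. The residual gap is an oral-arm participant who crosses over to injection and still has a perforation at 12 weeks.

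**Conclusion.** The point holds for SAE reporting. Section 10.4.1(b), as written, cannot be reconciled with 10.4.2 and Table 5, or with the commitments covering every SAR in 10.5.2 and 10.6.2. Followed literally, a related short-stay event gets no central causality or expectedness review; if it is also absent from the 6-week list, it may not reach BCTU at all.

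The size cannot be estimated, because the protocol gives no rate of short admissions or of related events. The conclusion rests on two assumptions: that sites apply 10.4.1(b) as worded, and, for glucose derangement, that they let it prevail over Table 5. It does not extend to a claim that the adverse event list is wrong or that the harms comparison between routes is biased.

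**What to change.** Reconcile 10.4.1, 10.4.2, 10.5.2 and 10.6.2 in one short amendment:

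- Limit 10.4.1(b) to hospital stays under 24 hours that the investigator judges unrelated to the intervention and that meet no other seriousness criterion.
- State that related events and Table 5 events follow 10.4.2 or 10.4.3 whatever the length of stay.

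The cost is the amendment, a note to sites and a few more SAE forms. No visit or assessment is added.

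Two optional additions could travel with it, as suggestions and not corrections: a glucose item on the 6-week AE list, and recording of the 12-week perforation finding in all arms using the otoscopy already scheduled for everyone. The glucose item would need a definition. The schedule contains no glucose test, so such an item would mainly pick up participants who already monitor their glucose.
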